## Abstract

Background: Research suggests the use of different forms of therapy as a way of decreasing dropout rates in the treatment of post-traumatic stress disorder (PTSD). The psychotherapies to be assessed in this study are trial-based cognitive therapy (TBCT), mindfulness-based health promotion (MBHP) and positive psychotherapy (PPT). Objectives: (1) to assess the online efficacy of TBCT compared to MBHP and PPT to reduce the symptoms of PTSD in the context of the Coronavirus Disease 2019 (COVID-19) pandemic; (2) to compare the efficacy of these psychotherapies in improving anxiety, depression, guilt and in promoting well-being; and (3) to describe how professionals perceive online treatment. Methods: A randomized, multicenter, single-blind clinical trial will be conducted, with three separate arms. An estimated sample of 135 patients will receive either TBCT, MBHP or PPT and will be treated through online, individual, weekly visits, totaling 14 sessions. The primary outcome will be CAPS-5 and secondary outcomes will be HADS and WHO-5. The variables used to mediate these outcomes will be the Trauma-Related Guilt Inventory (TRGI), Negative Core Beliefs Inventory (NCBI) and the California Psychotherapy Alliance Scale (CALPAS-P). Expected results: PTSD symptoms are expected to be reduced after TBCT, MBHP and PPT. No statistical difference is expected to be found among the three. Discussion: The present study will evaluate and contribute towards the development of new psychotherapeutic options for patients with PTSD. The results of this study will allow the dissemination of new effective and adaptable interventions for patients with PTSD.

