The Mindfulness-Based Stress Reduction (MBSR) program was created by Jon Kabat-Zinn and colleagues at the University of Massachusetts Medical Center in 1979, and it is an intervention whose effects on mental health and quality of life have produced several studies worldwide, both in clinical and non-clinical populations. Several protocols have been developed based on the MBSR aimed at specific populations, such as the Mindfulness-Based Health Promotion (MBHP) program developed by the Mente Aberta Brazilian Center for Mindfulness and Health Promotion. The MBHP program was inspired by the original MBSR model but adapted to the context of the Brazilian health care (SUS) system, addressing chronic conditions and mental disorders as well [36,37,38].

Positive psychology seeks to understand positive emotions, psychological potentialities and healthy human/social/institutional functioning, and apply this knowledge to help people and institutions, with a focus on the prevention and promotion of mental health [39]. At first, positive psychology focused a lot on happiness and subjective well-being [40,41]. In a second step, the studies gained a broader view of psychological well-being and another similar proposal entitled PERMA, which is composed of the following five spheres: *positive emotions*—*P; engagement*—*E; relationships*—*R; meaning*—*M; achievement*—*A* [42,43]. Although positive psychology aims to be a way of looking at life, some psychotherapeutic proposals, such as positive psychotherapy (PPT), have been developed, and clinical studies have been replicated in different clinical and cultural contexts [44,45].

The proposed study is a randomized control trial comparing TBCT, MBHP and PPT to treat patients with PTSD due to traumatic exposure during the COVID-19 pandemic. Our hypotheses are that TBCT is at least as effective as MBHP and possibly more effective than PPT, considering that no studies were found assessing its efficacy in patients with PTSD.

Our primary objectives are to assess the efficacy of TBCT for patients with PTSD because of or during the COVID-19 pandemic and to compare its efficacy with that of MBHP and PPT, with all therapies delivered online in the same sample. Secondarily, we aim to quantitatively assess symptoms of depression, anxiety and guilt, as well as well-being and the strength of the therapeutic alliance.

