### 2.2. Hypotheses

According to the literature and the results of other clinical trials, we have elaborated the following hypotheses:

**Hypotheses 1** **(H1)**.*TBCT and MBHP in online modalities are statistically different from PPT online in reducing the symptoms of PTSD*;

**Hypotheses 2** **(H2)**.
*TBCT and MBHP in online modalities are of greater effect size in reducing PTSD symptoms compared to the control (PPT);*

**Hypotheses 3** **(H3)**.*TBCT and MBHP in online modalities contain the largest effect sizes in reducing the symptoms of guilt over the traumatic event compared to the control*;

**Hypotheses 4** **(H4)**.*TBCT and MBHP in online modalities are statistically different from the control, with a larger effect size, in improving quality of life (or disability)*.

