### 2.15. Statistical Methods

The collected data will be analyzed statistically using the Statistics Package for Social Science software (SPSS), version 24.0 [77]. Clinical and demographic categorical variables will be analyzed with *X*^2^ (sex, education, color or race, and dropout rate) and continuous variables will be assessed with one-way ANOVA (age and scale scores). Missing data for both primary and secondary outcome measures will be analyzed by intention to treat (ITT) and multiple imputation (IM), with five imputed databases taking baseline and sociodemographic data and assuming the random chance mechanism. Generalized estimation equations (GHG), taking time as a covariate, will be performed to compare changes in scores over time and between groups (TCP, MBSR and PP). Effect sizes will be evaluated according to Cohen’s tests. The assumed level of statistical significance will be 0.05.

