## 4. Conclusions

We hope this study will shed light on the impact of the online use of the psychotherapies, herein evaluated, in the context of the pandemic and for mental health in general. This study was specifically designed for the current times and in accordance with the health standards for social distancing. We believe it will help patients diagnosed with PTSD, which seems to be among the most prevalent disorders caused by COVID-19. Results will also help increase the body of evidence on the efficacy of TBCT, MBHP and PPT online, as these types of therapy are increasingly being used but still lack evidence.

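### The abstract expects no difference among the three arms, section 2.2 expects TBCT and MBHP to differ from PPT, and the trial is sized and tested only for a difference

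*Protocol article*

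**What the plan says.** The protocol article states its expected primary result in three places.

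- **Abstract, expected results:** "PTSD symptoms are expected to be reduced after TBCT, MBHP and PPT", followed by "No statistical difference is expected to be found among the three".
- **Section 1, Introduction:** "Our hypotheses are that TBCT is at least as effective as MBHP and possibly more effective than PPT".
- **Section 2.2, H1:** "TBCT and MBHP in online modalities are statistically different from PPT online in reducing the symptoms of PTSD". H2 adds a larger effect for TBCT and MBHP and names PPT as the control.

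Section 2.10 sizes the trial with a between-group F test in a repeated-measures ANOVA. Section 2.15 plans generalized estimating equations to compare changes over time and between groups: "The assumed level of statistical significance will be 0.05". No equivalence or non-inferiority margin is given. Section 2.13 allocates patients 1:1:1 to three active therapies, so there is no untreated, waitlist or usual-care arm.

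On what will be concluded, the abstract says: "The results of this study will allow the dissemination of new effective and adaptable interventions for patients with PTSD". Section 4 says: "Results will also help increase the body of evidence on the efficacy of TBCT, MBHP and PPT online".

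**The concern.** For CAPS-5, the abstract's prediction and H1 cannot both be right. As the text stands, a significant result agrees with section 2.2 and a non-significant one agrees with the abstract, so no result counts against the stated expectations.

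The null side is the weak one. A difference test that fails to reject does not show that the arms are alike, and nothing in the design defines how alike would be alike enough. The same gap lies behind the introduction's claim about TBCT and MBHP, which is non-inferiority wording without a margin.

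If a null result came with falls in CAPS-5 in all arms, the abstract's two expectations would appear met, and the announced message of effective therapies would seem to follow. The data could not carry that message: without an untreated arm, change within an arm mixes treatment effect with natural recovery and regression to the mean.

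**Working it through.** **1. What the stated sample size tests.** Inputs from section 2.10: f = 0.25, alpha 0.05, power 0.80, k = 3 groups, m = 3 measures, correlation 0.50.

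- Noncentrality = f² × N × m / (1 + (m − 1) × correlation) = 0.0625 × 108 × 3 / 2 = 10.125.
- With 2 and 105 degrees of freedom, critical F = 3.08 and power = 0.809. At N = 105 power is 0.797, so 108 is the smallest balanced size. The plan's figure is reproduced.
- The group-by-time interaction version of the same calculation would give 36. The stated 108 is therefore the between-group difference test across the three measures, with no margin in it.

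**2. Evaluable patients.** 135 × 0.75 = 101.25, or 33.75 per arm (about 34).

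**3. Chance of a non-significant omnibus test when the arms truly differ.**

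| True f | N = 108 | about 101 evaluable |
|---|---|---|
| 0.25 | 19% | 22% |
| 0.20 | 39% | 42% |
| 0.15 | 63% | 65% |
| 0.10 | 81% | 82% |

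**4. What a non-significant pairwise result leaves open.** Half-width of the 95% interval at one time point, in SD units:

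- Baseline-adjusted, correlation 0.50 (variance factor 1 − 0.25 = 0.75): 1.96 × √(2 × 0.75 / 33.75) = 0.41.
- Unadjusted: 1.96 × √(2 / 33.75) = 0.48.
- If all 45 randomized per arm contributed fully: 0.36 and 0.41.

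If TBCT and MBHP are equal and both differ from PPT, f = 0.25 means a gap of 0.25 × 3 / √2 = 0.53 SD. An estimate near zero would exclude that gap. An estimate above 0.53 − 0.41 = 0.12 SD (adjusted) or 0.53 − 0.48 = 0.05 SD (unadjusted) would not, yet it stays non-significant up to 0.41 or 0.48 SD.

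**5. Could the planned size support a margin?** The article gives none, so 0.5 SD is assumed, with true difference zero and one-sided alpha 0.025.

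- Power per pair with 33.75 per arm = Φ(0.5 / SE − 1.96). Unadjusted: SE = 0.243, power 54%. Baseline-adjusted: SE = 0.211, power 66%.
- On the more favourable three-measure average, with 36 per arm, power is 74%.
- For 80% power, 42 to 63 evaluable per arm are needed at 0.5 SD, 66 to 99 at 0.4 SD and 117 to 175 at 0.3 SD. The range runs from the three-measure average to one unadjusted time point.

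**The case against.** The strongest reply is that section 2.2 is the section headed as hypotheses, that it agrees with the sizing, and that one loose sentence in an abstract does not spoil a valid superiority trial. Much of this stands. A significant result for TBCT or MBHP over PPT would be sound, and choosing active comparators is legitimate because the abstract's first objective is comparative. The reply does not remove the conflict, though. Both predictions are current text, and a separate analysis plan would not alter what the article has announced.

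Several stronger readings are tempting but not supported:

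- **Three incompatible hypotheses.** The introduction's version is compatible with H1 and H2, which say nothing about TBCT against MBHP. There is one clash, abstract against section 2.2, plus one claim without a margin.
- **A null result is likely even if a difference exists.** Not at the planned effect, where the chance is 19% to 22%. It becomes more likely than not only for effects well below plan.
- **A null will be read as proof that all three therapies work.** No decision rule says so. The wording of the abstract and section 4 only makes such a reading easy.
- **No arm has support in PTSD.** Sections 1 and 2.7 cite TBCT as effective in PTSD, from a 95-patient randomized comparison with prolonged exposure that found no significant difference on the primary outcome. Section 2.7 reports no PTSD studies for MBHP, and the introduction appears to say the same of PPT.
- **Regression to the mean explains the falls.** Selection is on PCL-5 and the outcome is CAPS-5, which weakens this effect but does not remove it.
- **Inflated family error.** Two unadjusted contrasts against PPT would give 9.1% and all three pairs 12.2%, but the article never specifies such tests, and multiplicity is commonly left to the analysis plan.

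**Conclusion.** Wrong as written; should be fixed, but not disqualifying. The article predicts both a difference from PPT and no difference among the arms, and only the first matches the sized test. A non-significant result would be inconclusive: pairwise intervals of ±0.41 to ±0.48 SD, and an omnibus miss rate of 22% at f = 0.25 and 65% at f = 0.15. The planned size does not give 80% power for a non-inferiority margin of 0.5 SD or smaller. Falls in CAPS-5 within all arms cannot on their own establish efficacy.

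The figures assume 25% loss from 135, equal arms, a correlation of 0.50 and normal approximations for the pairwise results. The margins are illustrative, since the article states none. The conflict between the abstract and section 2.2 depends on none of these figures.

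**What to change.** 1. Make superiority over PPT, as in section 2.2, the single primary hypothesis. Test it with the between-group comparison that section 2.10 sizes, and delete the no-difference prediction from the abstract.
2. Report TBCT versus MBHP as an estimated difference with a 95% confidence interval, and replace the introduction's at-least-as-effective wording.
3. State in section 2.15 that a non-significant result is inconclusive and not evidence of equal efficacy, and that within-arm change will not be reported as efficacy. Limit the abstract and section 4 to conclusions between arms.

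The cost is wording and narrower claims, with no added patients or arms. That holds only for this route. Moving the primary test to pairwise contrasts at the final assessment alone would leave power of about 59% (unadjusted) to 71% (baseline-adjusted) at 0.53 SD with about 34 per arm, and a formal margin for TBCT versus MBHP would need more patients, as shown above. Either choice would require the sample size to be redone.

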## 1. Introduction

According to the American Psychiatric Association (DSM-5) [1], post-traumatic stress disorder (PTSD) occurs after exposure to one or more traumatic events, including actual or threatened death, serious injury or sexual violence in situations such as direct experience of the traumatic event, witnessing as it occurs to others or learning about a violent or accidental traumatic event that happened to a family member or close friend. Furthermore, in accordance with the DSM-5, experiencing repeated or extreme exposure to aversive details of the traumatic events may provoke PTSD.

Although exposure to traumatic events is a global problem that carries the risk of producing PTSD [2], the vast majority of people have a brief acute stress response. Around 80% of people recover in the first month after the event without long-term consequences [3]. While epidemiological studies indicate prevalence rates ranging from 3.8% to 8.3% in the general population [4], this prevalence varies from 14.8% to 83% in people working during emergencies, such as physicians and nurses [5,6,7].

With the COVID-19 global crisis, the literature and experience in health care indicate that lasting emotional trauma can arise on an unprecedented scale [8], with devastating consequences such as unemployment, deaths and social isolation. Exposure to a serious illness leads to feelings of vulnerability, fear, panic and despair. No previous catastrophic events may be compared to the COVID-19 pandemic in terms of geographical scale [9]. World Wars I and II and other pandemics, for example, were geographically limited, saving some continents [10]. The Spanish flu, with high mortality rates in the first decades of the twentieth century, did not disseminate on a global scale. Furthermore, there is limited literature to help people deal with traumatic events, such as quarantine, mass disaster and ongoing stressors, making the damage to mental health on a large scale seem imminent. People who are quarantined are very likely to develop a wide range of symptoms of psychological stress and disorder, including depression and post-traumatic stress symptoms [11].

Thus, it is pertinent to look for effective psychotherapeutic interventions for people with PTSD that can be implemented online, facilitating the immediate availability of mental health care, regardless of the geographic region. Because of the empirical support that cognitive behavioral therapy (CBT) [12,13,14,15] and prolonged exposure therapy (PE) [16,17,18] have received, they are currently the first-line treatments for PTSD [19].

Available PTSD treatments have been shown to have a high non-response and dropout rate. A review of the literature of 55 studies of PTSD patients found non-response rates as high as 50% and dropout rates ranging widely and depending on the nature of the study population [20]. In a meta-analysis assessing war trauma [21], dropout rates ranged from 5% to 78%, and in a recent review of data from three clinical trials of evidence-based PTSD treatments in military service members, the dropout rate was 31% [22]. These findings suggest new and innovative strategies are needed to improve treatment retention, especially in a new and complex situation such as the COVID-19 pandemic. Thus, testing treatments for PTSD with lower potential for dropouts might still be necessary [23,24]. Recently, Duran et al. [25] showed that TBCT had a low dropout rate in PTSD relative to PE.

TBCT [26,27,28] is a novel and innovative transdiagnostic approach [29] shown to be effective for depression [30], social anxiety disorder [31,32,33,34], PTSD [25] and obsessive-compulsive disorder (Rodrigues et al., accepted). TBCT differs from other CBT approaches in that it introduces a new, organized and systematic approach to change dysfunctional negative core beliefs (CBs), while allowing cognitive, emotional and experiential work to be done conjointly [28]. While incorporating a courtroom metaphor to challenge dysfunctional CBs conceptualized as self-accusations, TBCT is an example of assimilative psychotherapy integration that relies on Beckian CBT, incorporating and integrating components of other psychotherapies [28,35].

The Mindfulness-Based Stress Reduction (MBSR) program was created by Jon Kabat-Zinn and colleagues at the University of Massachusetts Medical Center in 1979, and it is an intervention whose effects on mental health and quality of life have produced several studies worldwide, both in clinical and non-clinical populations. Several protocols have been developed based on the MBSR aimed at specific populations, such as the Mindfulness-Based Health Promotion (MBHP) program developed by the Mente Aberta Brazilian Center for Mindfulness and Health Promotion. The MBHP program was inspired by the original MBSR model but adapted to the context of the Brazilian health care (SUS) system, addressing chronic conditions and mental disorders as well [36,37,38].

Positive psychology seeks to understand positive emotions, psychological potentialities and healthy human/social/institutional functioning, and apply this knowledge to help people and institutions, with a focus on the prevention and promotion of mental health [39]. At first, positive psychology focused a lot on happiness and subjective well-being [40,41]. In a second step, the studies gained a broader view of psychological well-being and another similar proposal entitled PERMA, which is composed of the following five spheres: *positive emotions*—*P; engagement*—*E; relationships*—*R; meaning*—*M; achievement*—*A* [42,43]. Although positive psychology aims to be a way of looking at life, some psychotherapeutic proposals, such as positive psychotherapy (PPT), have been developed, and clinical studies have been replicated in different clinical and cultural contexts [44,45].

The proposed study is a randomized control trial comparing TBCT, MBHP and PPT to treat patients with PTSD due to traumatic exposure during the COVID-19 pandemic. Our hypotheses are that TBCT is at least as effective as MBHP and possibly more effective than PPT, considering that no studies were found assessing its efficacy in patients with PTSD.

Our primary objectives are to assess the efficacy of TBCT for patients with PTSD because of or during the COVID-19 pandemic and to compare its efficacy with that of MBHP and PPT, with all therapies delivered online in the same sample. Secondarily, we aim to quantitatively assess symptoms of depression, anxiety and guilt, as well as well-being and the strength of the therapeutic alliance.

## 2. Materials and Methods

### 2.1. Study Design

This study project is a randomized single-blind control trial with three parallel groups. After sample selection, patients with PTSD that developed or recurred as a consequence of the COVID-19 pandemic will be randomly assigned to TBCT, MBHP or PPT, with all therapies delivered online. Figure 1 shows the flowchart of the study. The duration of treatment will be 14 to 17 weeks, with a follow-up of 3, 6 and 12 months. The online psychotherapies will be carried out individually and weekly, totaling 14 one-hour sessions. Outcome measures will take place before session 1, session 7 and session 14, as well as at 3, 6 and 12 months. This study protocol was written following the standard protocol items, recommendations for interventional trials (SPIRIT) [46], has been registered on Clinicaltrials.gov (NCT04852770) and approved by the Ethics Committee of Maternidade Climério de Oliveira at Federal University of Bahia, Brazil. This study was funded by the National Council for Scientific and Technological Development (CNPq).

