### 2.7. Interventions

The three psychotherapeutic group interventions will be delivered through Skype or Google meeting platforms as weekly, one-hour long sessions, totaling 14 sessions (14 to 17 weeks). The sessions will be audiotaped in order to assure reliability in the fidelity of the intervention and to allow review by qualified supervisors.

Trial-based cognitive therapy

TBCT is a psychotherapeutic intervention whose foundation lies on Beckian CBT [28,50]. Although TBCT, like CBT, includes psychoeducation, cognitive restructuring and behavior experiments assigned as homework, it differs from other CBT approaches in terms of formulation (e.g., TBCT conceptualization diagram), techniques (e.g., participation grid to deal with guilt) and measurement instruments, such as the Cognitive Distortions Questionnaire (CD-Quest) [51] and the Negative Core Beliefs Inventory (NCBI) [52], making TBCT a distinctive approach in restructuring cognition at the three levels of cognition, especially in modifying the dysfunctional negative CBs of patients.

The main TBCT technique, The Trial, was inspired by Kafka’s novel “The Trial” [53]. It was designed to challenge and restructure dysfunctional CBs. A parallel with the CBT perspective is proposed by de Oliveira [54], who argues that the self-accusations presented by the novel’s character, Joseph K., might correspond to the dysfunctional negative CBs about the self. Like Joseph K., patients are not aware of these CBs/self-accusations, but after an investigation by means of the downward arrow approach, the patients become aware of such CBs/self-accusations and learn how to build a proper defense for themselves [54]. The Trial technique includes several CBT components (e.g., examining the evidence) and the empty-chair procedure [55,56], which makes TBCT more experiential [57].

Several studies support the efficacy of TBCT. In the first and preliminary study (*N* = 30) with patients presenting with different diagnoses, this treatment effectively decreased the patients’ attachments to dysfunctional negative CBs, as well as the emotional intensity, during a session [26]. This study [57] was replicated with 166 patients with varying diagnoses and comorbidities, showing a significant reduction in the attachment to dysfunctional CBs and in emotional intensity.

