### 2.8. Outcomes

Primary outcomes will be assessed by the reduction in PTSD symptoms, measured through CAPS-5. Secondary outcomes will be the improvement in symptoms of anxiety, depression and well-being. Mediator variables will also be assessed, measuring negative CBs, guilt and the strength of the therapeutic alliance. All scales will be applied by a blind assessor to the intervention groups before randomization (Initial Assessment), after seven sessions (Intermediate Assessment) and after 14 sessions (Final Assessment). They will also be applied in the 3-, 6- and 12-month follow-ups. Table 1 shows the flow of sessions and evaluations over the study period. Table 1 shows the SPIRIT diagram.

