### 2.9. Instruments

Diagnostic assessment

Structural Clinical Interview for the DSM-5 (SCID-5) [63]: It is a semi-structured psychiatric interview, with the purpose of providing a diagnosis, according to the Diagnostic and Statistical Manual of Mental Disorders (DSM-5).

*PCL-5 PTSD Check List 5:* It contains 20 items with the purpose of assessing PTSD symptoms, in accordance with criteria B, C, D and E (DSM-5). Each item is scored on a scale that ranges from 0 (not at all) to 4 (extremely) [47,48,49]. This scale will be applied only at intake.

Primary outcome

Clinician-Administered PTSD Scale (CAPS-5) [64]: It is a diagnostic interview scale with 30 items to assess the diagnosis and severity of PTSD symptoms in accordance with DSM-5 [65,66]. CAPS-5 will be applied at baseline, mid-treatment (session seven) and post-treatment (session fourteen), as well as at follow-up (3, 6 and 12 months).

Secondary outcome

*Hospital Anxiety and Depression Scale* (HADS) [65]: This is a 14-item scale used to determine anxiety and depression symptoms, where each item is worth 0 to 3 points, and a total score of 9 or higher suggests mild symptoms. It was translated and validated for the Brazilian population [67,68]. This scale will be administered at baseline (initial evaluation), mid-treatment (week 7) and post-treatment (week 14), as well as at 3-, 6- and 12-month follow-ups.

*The World Health Organization Five Well-Being Index (WHO-5):* This is an overall well-being scale, with five questions and scores ranging from 0 to 5, addressing mood and energy [69,70]. The WHO-5 validation study into Brazilian Portuguese included 1128 individuals. During this research, the instrument presented good internal validity (Cronbach’s alpha = 0.83) [71]. WHO-5 will be applied at baseline, mid-treatment (session seven) and post-treatment (session 14), as well as at the follow-ups (3, 6 and 12 months).

Mediator variables

Trauma-Related Guilt Inventory (TRGI) [72]: This is a 32-item questionnaire assessing the cognitive and emotional aspects of guilt that are associated to a specific traumatic event. TRGI will be applied at baseline, mid-treatment (session 7) and post-treatment (session 14), as well as at the follow-ups (3, 6 and 12 months).

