Negative Core Beliefs Inventory (NCBI) [52]: This inventory is designed to assess negative CBs, as described by [73]. It consists of 50 items evaluating beliefs about oneself and the world, on a Likert scale of 1 to 4 points each. NCBI will be applied at baseline, mid-treatment (session seven) and post-treatment (session 14), as well as at the follow-ups (3, 6 and 12 months).

*California Psychotherapeutic Alliance Scale—patient version (CALPAS-P):* Scale that assesses four dimensions of the therapeutic relationship [74,75]: (1) therapeutic alliance, (2) working alliance, (3) understanding and (4) therapist involvement, based on an agreement between patient and therapist about the goals of therapy. The CALPAS-P has 24 items ranging from 1 (never) to 7 (always) on the Likert scale. This scale will be administered at the end of second, fourth, sixth, eighth, tenth, twelfth and fourteenth psychotherapy sessions.

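### The mid- and post-treatment CAPS-5 is tied to session counts in the text but to weeks 7 and 14 in Table 1, and under the session wording a patient who stops therapy early has no defined assessment

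*Protocol article*

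**What the plan says.** Section 2.8 of the protocol article defines the primary outcome: "Primary outcomes will be assessed by the reduction in PTSD symptoms, measured through CAPS-5". Its timing is given in several places.

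- Section 2.1: "Outcome measures will take place before session 1, session 7 and session 14", followed by the 3-, 6- and 12-month visits.
- Section 2.8, for all scales: "after seven sessions (Intermediate Assessment) and after 14 sessions (Final Assessment".
- Section 2.9, CAPS-5 entry: "CAPS-5 will be applied at baseline, mid-treatment (session seven) and post-treatment (session fourteen".
- Section 2.9, HADS entry: "mid-treatment (week 7) and post-treatment (week 14".
- Table 1: the CAPS-5 row is marked under 7 weeks and 14 weeks.

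Treatment length is flexible. Section 2.1 states "The duration of treatment will be 14 to 17 weeks, with a follow-up of 3, 6 and 12 months", and Section 2.7 describes weekly sessions "totaling 14 sessions (14 to 17 weeks". Section 2.15 promises an intention-to-treat analysis with multiple imputation, and generalised estimating equations with time as a covariate.

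For the alliance scale CALPAS-P, Section 2.9 says "This scale will be administered at the end of second, fourth, sixth, eighth, tenth, twelfth and fourteenth psychotherapy sessions". Table 1 marks it at baseline, 7 weeks and 14 weeks.

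**The concern.** Session 14 and week 14 are the same moment only for a patient who never misses a week. The article allows up to three further weeks, so the post-treatment CAPS-5 can follow different amounts of therapy depending on which section site staff use. The anchor also settles what time means in the Section 2.15 model.

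A session anchor has a further weakness: it exists only for patients who attend that session. The article's own rationale is that dropout differs between therapies (Sections 1 and 2.7), and Section 2.15 compares dropout across arms. If outcomes are lost when therapy stops, the loss may therefore differ by arm. The imputation is described as drawing on baseline and sociodemographic data. A CAPS-5 actually observed after stopping would carry more information than a value imputed from those.

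**Working it through.** The plan gives no figure for this gap, so there is none to reproduce. The check sets the schedules side by side and then counts sessions.

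**1. The schedules that apply**

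| Place | Mid-treatment | Post-treatment | Anchor |
|---|---|---|---|
| Section 2.1, outcome measures | before or at session 7 | before or at session 14 | session |
| Section 2.8, all scales | after 7 sessions | after 14 sessions | session |
| Section 2.9, CAPS-5 | session 7 | session 14 | session |
| Section 2.9, HADS | week 7 | week 14 | week |
| Table 1, CAPS-5 row | 7 weeks | 14 weeks | week |

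The conflict does not depend on how Section 2.1 is read. Section 2.8 and Table 1 both cover CAPS-5 and use different anchors.

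**2. Sessions received by week 14**

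Inputs: 14 sessions in a course of W = 14 to 17 weeks (Sections 2.1 and 2.7). At an even pace the count is 14 × 14/W. The minimum, when every skipped week falls before week 14, is 14 − (W − 14).

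| Course length W | Even pace | Minimum |
|---|---|---|
| 14 weeks | 14.0 | 14 |
| 15 weeks | 13.1 | 13 |
| 16 weeks | 12.3 | 12 |
| 17 weeks | 11.5 | 11 |

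The largest gap between a week-14 and an after-session-14 assessment is 17 − 14 = 3 weeks, or 14 − 11 = 3 sessions. The mid-treatment assessment shifts as well. At an even 17-week pace, week 7 falls after 14 × 7/17 = 5.8 sessions, and the seventh session falls at 7 × 17/14 = 8.5 weeks.

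**3. A patient who stops therapy**

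Take a patient who stops at session 5. Under Sections 2.1, 2.8 and the CAPS-5 entry in 2.9, neither session 7 nor session 14 occurs, so no mid- or post-treatment date is defined. A patient who stops between sessions 7 and 14 lacks only the post-treatment one. Under Table 1 both patients have dates at weeks 7 and 14. No section says which rule governs, or that patients who have stopped are still assessed. Multiple imputation fills in a missing score; it does not say when, or whether, an assessment is due.

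**4. CALPAS-P**

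Section 2.9 lists sessions 2, 4, 6, 8, 10, 12 and 14. Session 7 is not among them, so the 7-week mark in Table 1 has no counterpart. The baseline mark cannot be met: Sections 2.11 and 2.12 bring in the therapist only after baseline assessment and randomisation, so there is no alliance yet to rate.

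**The case against.** For weekly sessions, the column heads in Table 1 may be nominal labels for sessions 7 and 14. That is possible, but the article does not say so, and it uses weeks for HADS in the same section that uses sessions for CAPS-5. It is also true that nothing says assessment ends when therapy ends, that CAPS-5 is scheduled again at 3, 6 and 12 months, and that a condensed article may leave the handling of discontinued patients to the full protocol. These points soften the concern. They do not resolve two stated schedules that differ for the primary outcome. The 11-session figure is a worst case, and the same schedule applies to all arms.

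Several stronger readings are tempting but not supported:

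- A reader might infer that Section 2.1 fixes the final CAPS-5 after only 13 sessions. The sentence can equally mean before session 1, at session 7 and at session 14, which fits Section 2.9.
- A reader might see a baseline conflict between before session 1 (2.1) and before randomisation (2.8). The second implies the first, and Sections 2.8, 2.12 and 2.13 agree.
- A reader might apply the 25% dropout allowance to the 135 patients and count the result as patients with no primary outcome. Section 2.10 does not say whether that allowance means stopping therapy or loss to assessment.
- A reader might conclude that CALPAS-P will unblind the assessor. That requires the general statement on all scales in Section 2.8 to override the separate end-of-session schedule in Section 2.9, and no item wording is given to show that answers reveal the arm.

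**Conclusion.** The point holds as an inconsistency in when the primary outcome is measured. The post-treatment CAPS-5 has a session anchor in three sections and a week anchor in Table 1, and these differ by up to 3 weeks and 3 sessions within the permitted treatment window. Under the session wording, patients who stop early have no defined assessment at the anchors they never reach, which sits badly with the promised intention-to-treat analysis. Under Table 1 they do. It would therefore go too far to say that the plan excludes them or cannot deliver that analysis.

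The size rests on the stated 14 to 17 weeks and on a literal reading of Table 1. The article gives no basis for estimating bias in the treatment comparison, and the sample size is unaffected. The CALPAS-P mismatch is real but secondary. Both should be corrected; neither invalidates the design.

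**What to change.** - Reconcile Sections 2.1, 2.8, 2.9 and Table 1 to one anchor for the mid- and post-treatment CAPS-5 that every randomised patient can reach. One option is a fixed time from randomisation, with the post-treatment visit at the end of the permitted 17-week window.
- State that all randomised patients are assessed at that time, whether or not therapy continues.
- State the origin of the 3-, 6- and 12-month follow-ups so that they fall after the post-treatment assessment, for example by counting from it. Counted from randomisation, month 3 would be about week 13 (52/4) and would precede a week-17 visit.
- For CALPAS-P, remove the baseline mark and keep one schedule. As a precaution for blinding, exempt this scale from the Section 2.8 statement that a blinded assessor applies all scales.

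The cost is wording and one corrected table. The drawback is that patients who finish in 14 weeks, or who stop early, are measured some time after their last session: up to about three weeks for those who finish, and longer for those who stop early.
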